# Rivaroxaban in patients with abdominal aortic aneurysm and high-sensitivity C-reactive protein elevation (BANBOO): study protocol for a randomized, controlled trial

**DOI:** 10.1186/s13063-023-07461-3

**Published:** 2023-06-19

**Keywords:** Abdominal aortic aneurysm, High-sensitivity C-reactive protein, Rivaroxaban; Randomized controlled trial, Protocol

## Abstract

**Background:**

Abdominal aortic aneurysm (AAA) is a fatal disease due to the tendency to rupture. The drug treatment for small AAA without surgical indications has been controversial. Previous studies showed that high-sensitivity C-reactive protein (hs-CRP) had become a potential biomarker of the disease, and the anti-inflammatory effect of rivaroxaban for AAA had been well established. Thus, we hypothesized that rivaroxaban could control the progression of AAA in patients with hs-CRP elevation.

**Methods:**

The study is a prospective, open-label, randomized, controlled clinical trial. Sixty subjects are recruited from the General Hospital of Northern Theatre Command of China. Subjects are randomly assigned (1:1) to the intervention arm (rivaroxaban) or control arm (aspirin). The primary efficacy outcome is the level of serum hs-CRP at 6 months. The secondary outcomes include imaging examination (the maximal diameter of AAA, the maximal thickness of mural thrombus, and the length of aneurysm), major adverse cardiovascular and cerebrovascular events (MACCE, including AAA transformation, non-fatal myocardial infarction, acute congestive heart failure, stent thrombosis, ischemia-driven target vessel revascularization, vascular amputation, stroke, cardiovascular death, and all-cause death), and other laboratory tests (troponin T, interleukin 6, D-dimer, and coagulation function).

**Discussion:**

The BANBOO trial tested the effect of rivaroxaban on the progression of AAA in patients with elevated Hs-CRP for the first time.

**Trial registration:**

ChiCTR2100051990, ClinicalTrials.gov, registered on 12 October 2021.

**Supplementary Information:**

The online version contains supplementary material available at 10.1186/s13063-023-07461-3.

## Introduction

### Background and rationale {6a}

Abdominal aortic aneurysm (AAA) is a chronic progressive disease that occurs mainly among males above 65 [1]. The incidences of AAA for males and females over 60 years were shown to be 5% and 1% [2]. Smoking and hypertension could promote the rupture risk of an aneurysm. Mortality could rise to 50–80% once rupture [3]. The drug treatment for “small” AAA, defined as the maximal aortic external diameter between 30 and 55 mm, has been controversial for individuals without surgical indications [4]. There are two main controversial points: whether the progression of AAA can be delayed or prevented and whether the fatal rupture incidence of AAA can be reduced by medical treatment.

A large number of evidence indicate that aortic wall inflammation is pivotal to the pathogenesis of AAA [5]. Regulating the expression of inflammation-related genes is a promising strategy for inhibiting the progression of AAA. The inflammatory cytokine high-sensitivity C-reactive protein (hs-CRP) has been corroborated as a potential biomarker of AAA [5]. Hs-CRP has been verified to predict cardiovascular risk and holds a positive correlation with the size of AAA [6]. The progression, expansion, and rupture of AAA could be diminished successfully by the exogenous anti-inflammatory drug [7–9].

Studies have shown that the average level of hs-CRP decreased significantly by rivaroxaban treatment from baseline to the endpoint of research [10, 11]. In addition, for the pro-inflammatory activity of factor Xa in arterial thrombosis, the direct inhibition of factor Xa by rivaroxaban may particularly benefit antithrombosis [12]. Rivaroxaban inhibits tissue factors, which induce platelet aggregation [13]. Studies showed that factor Xa inhibitor rivaroxaban exerted anti-inflammatory and anti-oxidative stress effects in human AAA lesion, suggesting a role of factor Xa underlying the pathogenesis of AAA [14, 15].

Many preclinical studies suggested that rivaroxaban may have a beneficial effect on AAA [15]. There have been extensive randomized controlled trials (RCTs) to evaluate the safety and efficacy of rivaroxaban in cardiovascular and cerebrovascular diseases (stroke prevention, venous protection, and vascular protection) [16]. For example, in the EINSTEIN study [17, 18], the risk of a recurrent event was significantly lower in the rivaroxaban group (10 to 20 mg) than in the aspirin group, without a significant increase in bleeding events [19]. In the ATLASACS-TIMI46 study [20], the rivaroxaban group was superior in terms of net clinical outcomes (death, myocardial, stroke, or TIMI hemorrhage).

New oral anticoagulant rivaroxaban has the advantages such as convenient usage, predictable pharmacokinetic characteristics, no requirement for regular monitoring, accurate anticoagulant effect, and low risk of bleeding, especially intracranial hemorrhage [21]. However, no specific medical therapy has been recommended (III, A), due to absence of evidence showing the slowed expansion rate of an AAA [22]. Moreover, blood pressure control, statins, and antiplatelet therapy should be considered in all patients with AAA (IIa, B) [22]. Therefore, we chose aspirin as a comparator of rivaroxaban in this trial.

We hypothesized that rivaroxaban had a good control effect on the progression of AAA in patients with elevated hs-CRP. The BANBOO study, a randomized controlled trial, will test this hypothesis, and its results will guide clinical practice (Fig. 1).

**Fig. 1 Fig1:**
[figure not shown]
Study concept

### Objectives {7}

The primary objective is to explore the anti-inflammatory efficacy of rivaroxaban in the treatment of AAA with hs-CRP elevation and to investigate the application value of rivaroxaban for AAA. The secondary objectives are to analyze the safety of rivaroxaban for AAA and the efficacy of rivaroxaban on antithrombosis and alleviating inflammatory lesions.

### Trial design {8}

The BANBOO trial is a prospective, single-center, open-label, randomized, controlled clinical trial conducted in the General Hospital of Northern Theatre Command of China. The protocol was designed to adhere to the recommendations of the Standard Protocol Items for Randomized Trials statement (SPIRIT) [23–25]. The research flowchart of the BANBOO trial is detailed in Fig. 2.

**Fig. 2 Fig2:**
[figure not shown]
Research flowchart of the BANBOO trial

## Methods: participants, interventions, and outcomes

### Study setting {9}

Initial baseline assessment includes contact information, physical examination, vital signs, demographical data, previous history, clinical characteristics, admission diagnosis, imaging examination, and laboratory test data. Once a standardized interview is performed, the data will be recorded in each subject’s case report form (CRF). Follow-up visits will occur at entry, 1 month, and 6 months after treatment initiation, and outcome data will be collected. Detailed collecting information on visits is listed in Table 1. An imaging subgroup is set up to analyze the effect of rivaroxaban on AAA morphology. All subjects screened, regardless of whether they are eligible for randomization, are provided with follow-up calls twice at 1 month and 6 months. Any interruption of treatments due to personal reasons is required to report within 24 h. Treatment should be discontinued immediately for emergent situations, including trauma or urgent invasive procedures, for the benefit of subjects.

**Table 1 Tab1:** Collecting information on visits

Follow-up	Baseline (visit 1)	1 month (visit 2, ± 7 days)	6 months (visit 3, ± 7 days)
Inclusion/exclusion criteria	X		
Physical examination	X		
Vital signs	X		
ICF	X		
Contact information	X		
Demographic data	X		
Previous history	X		
Admitting diagnosis	X		
Subject guidance	X		
Drug therapy	X	X	X
hs-CRP	X	X	X
Imaging examination	X		X
MACCE		X	X
Other laboratory tests	X	X	X
Bleeding events (BARC)	X	X	X
Liver function	X	X	X
Renal function	X	X	X
Subject compliance		X	X

*ICF* inform consent form, *hs-CRP* high-sensitivity C-reactive protein, *MACCE* major adverse cardiovascular and cerebrovascular event, *BARC* Bleeding Academic Research Consortium

### Inclusion and exclusion criteria {10}

The BANBOO study is designed to enroll 60 AAA subjects with hs-CRP elevation. Subjects aged 18 to 85 years, 30–50 mm in diameter of the aneurysm, and serum hs-CRP ≥ 2 mg/L are eligible for enrollment. Each enrolled subject should provide written informed consent before randomization. Complete inclusion and exclusion criteria are listed in Table 2 and Table 3.

**Table 2 Tab2:** Inclusion criteria

Inclusion criteria
1. 18–85 years old
2. AAA diagnosed by CTA; the maximal diameter of aneurysm is 30–50 mm
3. Serum hs-CRP ≥ 2 mg/L
4. Written informed consent

*AAA* abdominal aortic aneurysm, *CTA* computed tomography angioplasty, *hs-CRP* high-sensitivity C-reactive protein

**Table 3 Tab3:** Exclusion criteria

Exclusion criteria
1. ACS (unstable angina and acute myocardial infarction)
2. Dual antiplatelet therapy for stable CHD less than 6 months after PCI or ACS less than 1 year after PCI
3. Acute congestive heart failure or left ventricular ejection fraction ≤ 40%
4. Suffered from infectious diseases within 2 months before screening and infection has not been controlled more than 1 month
5. Active hepatitis, the elevation of alanine aminotransferase (ALT) value > 5 × the upper limit of normal
6. Severe renal failure (CrCl < 30 ml/min)
7. Life expectancy is less than 1 year
8. Any situation may interfere with the research process, such as dementia, paralysis, alcoholism, etc
9. Pregnancy or women during the lactation period
10. Suffered from hereditary connective tissue disease, such as Marfan’s syndrome, etc
11. Known allergies or intolerance to aspirin or rivaroxaban
12. AAA tends to rupture or has ruptured, and abdominal pain aggravates
13. Major surgery within 1 month
14. Active stage of severe peptic ulcer or previous bleeding events (including retinal or vitreous hemorrhage, urinary tract hemorrhage, etc.) within 6 months
15. Have participated in other ongoing clinical studies
16. Refuse to provide a written informed consent
17. Other unsuitable conditions adjudicated by investigators

*ACS* acute coronary syndrome, *CHD* coronary heart disease, *PCI* percutaneous coronary intervention, *CrCl* creatinine clearance rate, CrCl = body weight(kg) × (140-age)/[0.818 × CREA(μmol/L)][serum creatinine (CREA) is tested by enzymatic method. Female: above data results × 0.85]

### Consent or assent {26a}

[name] and [name] are responsible for obtaining written informed consent from participants who meet the inclusion criteria but not the exclusion criteria and are willing to provide written informed consent.

### Interventions

#### Choice of comparator {6b}

The study used aspirin as a control group, as recommended by the AAA guidelines. In the control arm, aspirin (100 mg q.d., Aspirin Enteric-coated Tablets, Bayer) is started at the time of randomization for 6 months. Subjects also receive standard background therapy with pitavastatin (2 mg daily, LiQingZhi, Japan Kowa Co., LTD), according to clinical guidelines.

#### Description of intervention {11a}

In the intervention arm, rivaroxaban (15 mg q.d., Xarelto, Bayer) is applied at the time of randomization for 6 months; the rivaroxaban dose will be reduced to 10 mg q.d. for the subjects aged over 75 years old. Subjects also receive standard background therapy with pitavastatin (2 mg daily, LiQingZhi, Japan Kowa Co., LTD).

#### Criteria for discontinuing or modifying allocated intervention {11b}

Possible reasons for withdrawal include (but not limited to) the following: subject’s voluntary withdrawal; the doctor will withdraw the subject according to clinical indications; subjects were lost to follow-up. Other conditions that may lead to treatment suspension will be evaluated and determined by investigators. If the protocol or ICF needs to be amended, the researchers are required to submit the amendment to the ethics committee for approval. Approved protocols or ICF amendments will be available to researchers prior to implementation. If an overdose occurs during the study period, the investigator should immediately notify the study leader and the principal investigator within 24 h but no later than the second day.

#### Strategies to improve adherence to interventions {11c}

Investigators and monitors will be trained in the research program, CRF, and regimen of research drugs. All training must be documented, including the revision of training materials, trained members, and training dates. The purpose of the training was to emphasize the importance of timely medication to the subjects. In addition, researchers will contact subjects regularly by telephone, solve the problems raised by patients in time, and increase the compliance of patients. All drugs used in the BANBOO trial should be recorded in the appropriate location in the CRF.

#### Relevant concomitant care permitted or prohibited during the trial (11d)

Medications are recommended according to current clinical guidelines. If the subjects need to use other drugs, the doctors should be informed.

#### Ancillary and post-trial care {30}

All patients screened, regardless of whether they are eligible for randomization, are documented in the patient database of the trial center and provided with regular follow-up calls or face-to-face visits even post-trial. At the end of the trial, the subject’s attending physician will determine the subject should continue the treatment regimen.

### Outcomes {12}

The primary efficacy outcome is the level of serum hs-CRP at 6 months. The secondary outcomes include imaging examination (the maximal diameter of AAA, the maximal thickness of mural thrombus, and the length of aneurysm), major adverse cardiovascular and cerebrovascular events (MACCE, including AAA transformation, non-fatal myocardial infarction, acute congestive heart failure, stent thrombosis, ischemia-driven target vessel revascularization, vascular amputation, stroke, cardiovascular death, and all-cause death), other laboratory tests (troponin T, interleukin 6, D-dimer, and coagulation function). Blood will be taken at entry and 1 and 6 months to assess changes in circulatory indexes. CTA will be performed at entry and 6 months, depending on local ethics guidelines. The safety outcomes include bleeding events defined according to the Bleeding Academic Research Consortium criteria (BARC), liver function (determined by alanine aminotransferase), and renal function (determined based on the creatinine clearance rate). Detailed endpoints are listed in Additional file 1: Appendix A, and detailed definitions of endpoints are shown in Additional file 1: Appendix B. The results of the BANBOO trial will be interpreted based on all endpoints.

### Participant timeline {13}

The study is expected to last 18 months, including a 12 months enrollment period and a 6 months follow-up period.

### Sample size calculation {14}

Power calculations are based on a superiority comparison of the primary endpoint. Assuming the level of serum hs-CRP in the aspirin arm (control) is 4.79 ± 3.2 mg/L at 6 months, and taking the drop-out rate is 10%, 30 patients in each arm (60 in total) are planned to be enrolled and randomly assigned in a 1:1 ratio, to provide 90% power to detect a 2.54 mg/L absolute value reduction in rivaroxaban arm (intervention) in comparison with that in aspirin group with a 2-sided type I error of 0.05.

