## Statistical considerations

### Statistical methods for primary and secondary outcomes {20a}

The primary endpoint analysis will be performed according to the intention-to-treat principle. The main aim of this study is to investigate whether rivaroxaban is superior to aspirin in reducing the level of serum hs-CRP in patients with AAA and hs-CRP elevation at 6 months. The null hypothesis (H0) for this analysis is that the level of the primary endpoint in the intervention arm is the same as that of the control arm, namely P0 = P1. The alternative hypothesis (H1) is that the levels of the primary endpoint in the two arms is not equal, namely P0 ≠ P1, and the superiority test is conducted at the 2-sided significance level of 0.05.

Continuous variables are presented as the mean ± standard deviation or the median with interquartile range and compared between two arms via *T*-test or Mann–Whitney *U* test. Categorical variables are presented as counts and percentages and compared between two arms via *χ*^2^ test. Kaplan–Meier curves and Log-rank tests are used to describe the cumulative incidences of MACCE and bleeding events. The differences in the risk of AAA between the two arms are estimated using a Cox proportional hazards model. A two-sided *P* < 0.05 is considered to be statistically significant. All statistical analyses are performed using the SAS (Version 9.3) software.

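### The 90% power does not follow from the printed inputs: with the one SD given (3.2 mg/L) in both arms, 30 enrolled per arm gives about 82%

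*Protocol article*

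**What the plan says.** All the planning inputs are in the protocol article, section Sample size calculation {14}.

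- Control arm: "Assuming the level of serum hs-CRP in the aspirin arm (control) is 4.79 ± 3.2 mg/L at 6 months".
- Effect: the size is meant "to provide 90% power to detect a 2.54 mg/L absolute value reduction in rivaroxaban arm (intervention"), compared with the aspirin arm.
- Drop-out: "taking the drop-out rate is 10" per cent.
- Size: "30 patients in each arm (60 in total) are planned to be enrolled and randomly assigned in a 1:1 ratio".
- Error rate: "with a 2-sided type I error of 0.05", with power stated as 90%.

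The section Statistical methods for primary and secondary outcomes {20a} fixes the same error rate for the analysis: "the superiority test is conducted at the 2-sided significance level of 0.05". It names a t-test or a Mann–Whitney U test for continuous outcomes.

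No SD is given for the rivaroxaban arm, and 3.2 mg/L is nowhere called common or pooled.

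**The concern.** A reader who is given one SD and one difference will normally use that SD for both arms. Doing so here does not return 90% power at 30 per arm, and the gap is too wide to be rounding or a choice of formula. So either the stated power is wrong, or an input that decides the answer is missing from the sentence.

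This sentence is the statistical justification for the number of patients on the primary endpoint; the Discussion adds only the centre's admission volume. If 3.2 mg/L does apply to both arms, the chance of missing a true 2.54 mg/L difference is about 18%, not the 10% that the stated power implies. A non-significant result would then be taken as stronger evidence against an effect than the design can give.

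**Working it through.** **Inputs** (all from Sample size calculation {14}): difference d = 2.54 mg/L; control mean 4.79 and SD 3.2 mg/L; two-sided α = 0.05; power 90%; drop-out 10%; 30 enrolled per arm. The implied rivaroxaban mean is 4.79 − 2.54 = 2.25 mg/L. Evaluable patients per arm: 30 × 0.9 = 27.

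**Step 1. Try to reproduce 30 per arm, with SD 3.2 in both arms.**

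n per arm = 2(z₀.₉₇₅ + z₀.₉₀)² SD² / d² = 2 × (1.960 + 1.282)² × 3.2² / 2.54² = 33.35, so 34 evaluable. The noncentral t gives 35. After drop-out: 34/0.9 = 37.8, so 38; 35/0.9 = 38.9, so 39. The stated 30 is not reproduced.

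**Step 2. Power at the planned size, SD 3.2 in both arms.**

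Standard error = 3.2 × √(2/n). At n = 27 it is 0.871, and 2.54/0.871 = 2.916. By normal approximation, power = Φ(2.916 − 1.960) = 83.1%.

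| Analysed per arm | Normal approximation | t-test (noncentral t) |
|---|---|---|
| 27 (10% drop-out) | 83.1% | 81.7% |
| 30 (no drop-out) | 86.7% | 85.6% |

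The second row also bounds what imputing missing values could add: even 30 fully observed patients per arm fall short of 90%.

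**Step 3. What 27 per arm can detect with 90% power, SD 3.2 in both arms.**

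Normal approximation: (1.960 + 1.282) × 3.2 × √(2/27) = 2.82 mg/L. With the t-test it is 2.88 mg/L.

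**Step 4. What would make the 90% true with a two-sided 5% test and 27 per arm.**

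Keep 3.2 in the aspirin arm and let the rivaroxaban SD be s: n = (3.2² + s²)(1.960 + 1.282)² / 2.54². Power by t-test uses the same variance sum and 52 degrees of freedom.

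| Rivaroxaban SD s | n by formula | Evaluable, then enrolled per arm | Power at 27, normal | Power at 27, t-test |
|---|---|---|---|---|
| 2.4 | 26.06 | 27, then 27/0.9 = 30 | 91.0% | 89.9% |
| 2.5 | 26.86 | 27, then 27/0.9 = 30 | 90.2% | 89.1% |
| 3.2 | 33.35 | 34, then 38 | 83.1% | 81.7% |

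The largest s that still gives 90% at 27 per arm is 2.52 by the normal formula and 2.39 by the t-test. If the SD is instead the same in both arms, it could be at most 2.88 (normal) or 2.83 (t-test).

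**Step 5. The one-sided alternative.**

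With a one-sided 5% test and SD 3.2 in both arms: 2 × (1.645 + 1.282)² × 3.2² / 2.54² = 27.19, so 28 evaluable and 31 to 32 enrolled, depending on how drop-out is added (28 × 1.1 = 30.8; 28/0.9 = 31.1). It reaches 30 only if 27.19 is left unrounded and 27.19/0.9 = 30.2 is then rounded down. Power at 27 per arm would be 89.8% (normal) or 89.1% (t-test).

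**The case against.** The strongest reply is that 3.2 mg/L belongs to the aspirin arm only, and that carrying it over to rivaroxaban is the reviewer's step. At an implied mean of 2.25 mg/L, an SD of 3.2 is a coefficient of variation of 3.2/2.25 = 1.42, against 3.2/4.79 = 0.67 in the control arm, for a marker that cannot go below zero. A smaller SD is therefore plausible. If the coefficient of variation were the same in both arms (an assumption the article does not make), the rivaroxaban SD would be about 0.67 × 2.25 = 1.5 and power at 27 per arm about 96%. The published article is also a condensed account, and the full protocol may give a second SD.

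This stands as far as it goes: the shortfall is conditional on a common SD. It does not dispose of the point. The sentence prints power, size, difference, drop-out and error rate as a complete calculation, and the only SD in it does not yield the stated power when used for both arms. The reader cannot tell which assumption was made, and the power at 27 per arm runs from about 82% to about 96% over the SDs considered here.

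A reader might infer that the size was really computed with a one-sided 5% test. The documents do not support that. Both relevant sections say two-sided, and a two-sided test with a rivaroxaban SD of 2.4 to 2.5 gives exactly 27 evaluable and 30 enrolled, a closer match than the one-sided route.

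It can also be said that type I error and the analysis are untouched, that recruitment began in October 2021, and that a null result should be judged by its confidence interval. That limits the seriousness of the point, but it does not make the printed figure right.

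**Conclusion.** The stated 90% power does not follow from the inputs as printed. With SD 3.2 mg/L in both arms, a 2.54 mg/L difference, two-sided 5% and 10% drop-out, the planned size gives about 82% (t-test) or 83% (normal approximation), and about 86% with no loss at all. Under the same assumptions, 90% needs 34 to 35 evaluable patients per arm, or 38 to 39 enrolled.

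The result rests on a common SD, which the article neither states nor excludes. A reader might go further and conclude that the trial certainly has only 82% power; that is not shown, because a rivaroxaban SD of about 2.4 to 2.5 mg/L or less would restore the 90%. What is established is that the sentence either misstates the power or omits the SD on which it depends. This is a reporting correction of moderate weight and gives no ground for changing the number of patients.

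**What to change.** Keep 60 patients and correct the sentence in Sample size calculation {14}. First settle which SD was used for the rivaroxaban arm, then:

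- If 3.2 mg/L was meant for both arms, restate the power: 30 enrolled (27 evaluable) per arm gives about 82% power for 2.54 mg/L at two-sided 5%, or 90% power for about 2.9 mg/L.
- If a smaller rivaroxaban SD was used, state it and the formula, say that the 90% depends on it, and give the roughly 82% under a common SD of 3.2 alongside.

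The order matters: writing 82% without checking could replace a correct figure with a wrong one. The cost is one sentence and a less favourable stated power.
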